### Criteria for discontinuing or modifying allocated interventions

The intervention will be discontinued for participants in case of the occurrence of exclusion criteria and participants’ requests.

### Sample size

The sample size required to investigate and compare the outcomes of the study between the three groups was calculated by considering these items: due to the limited literature regarding the impact of *Pistacia atlantica* on antioxidant capacity in humans and citing the calculations from researcher’s own experiences about similar oils, the minimal effect size of 0.10–0.13 as a conservative average was considered for primary outcomes [30]. Also, a correlation between repeated measures as a conservative average was considered 0.5. The power and confidence interval for these calculations were considered as 0.80 and 0.95, respectively. Calculations were done using GPower 3.1.4.9. Therefore, the sample size for each treatment oil period was estimated to be 21 subjects; with taking a 10% of dropout, we required at least 24 people for each intervention period. Based on this calculation, 72 eligible participants will be entered into the current study. We will also calculate the power of this trial using a conservative estimate of a medium effect size.

Due to the limited literature regarding the impact of *Pistacia atlantica* on antioxidant capacity in humans and citing the expert’s opinion, the effect size [standardized mean difference (SMD)] was considered to be at least one. Based on this, considering the first type error of 5% and power of 80% and using the table of sample sizes calculated for factorial studies [31], the sample size in each group was estimated to be 21 subjects, which takes into account the 10% drop, requires at least 24 people in each intervention period. Based on this calculation, 72 eligible participants will be entered into the current study.

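### Two unreconciled effect sizes both lead to 21, 24 and 72 by parallel-group logic that does not fit the cross-over; if 0.10–0.13 is Cohen's f or an SMD, 72 participants give less than 80% power

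*Protocol article*

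**What the plan says.** All of the following is in the Sample size section of the protocol article.

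- **First paragraph.** The planning value is given as "the minimal effect size of 0.10–0.13 as a conservative average was considered for primary outcomes". The paragraph continues that "a correlation between repeated measures as a conservative average was considered 0.5" and that "The power and confidence interval for these calculations were considered as 0.80 and 0.95, respectively". The software is named ("Calculations were done using GPower 3.1.4.9"), but the test family, the number of measurements and the metric of the effect size are not. The result is that "the sample size for each treatment oil period was estimated to be 21 subjects", and "with taking a 10% of dropout, we required at least 24 people for each intervention period". The total is 72. The paragraph ends by promising a further power calculation at a medium effect size.
- **Second paragraph.** Here "the effect size [standardized mean difference (SMD)] was considered to be at least one". The text goes on "considering the first type error of 5% and power of 80" per cent, reads the answer from a table for factorial studies, and again reports 21 per group, 24 after dropout and 72 in total.

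Study design and population describes a three-way cross-over. Blinding, randomization, and allocation concealment assigns each participant to one of six orders of the same three oils.

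**The concern.** Two planning assumptions that look very different produce the same number, and the text does not say which one governs. One is described as minimal and conservative. The other, an SMD of at least one, is a large effect. The step from 24 per period to 72 also multiplies by the number of oils, as if each oil had its own group of people. In the design described, each period contains all 72 participants.

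This is the only stated basis for 72 and for 80% power. The Discussion builds on it when it claims high power for sex-stratified effects and enough power for gene-diet interactions. If the trial was meant to detect a small effect and has well under 80% power for it, a null result could be misread as evidence that the oils do not differ. If it was meant to detect an SMD of one, the trial is several times larger than that aim needs.

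**Working it through.** **Inputs.** From the Sample size section: effect size 0.10–0.13 or SMD 1, correlation ρ = 0.5, power 0.80, alpha 0.05, dropout 10%, total 72. From the design sections: three oils per participant (m = 3), measured at the start and end of each period. Completers: 72 × 0.9 = 64.8, taken as 65. My assumptions: two-sided 5% level, sphericity, ρ applying between a participant's values under the three oils, and no adjustment across the nine primary markers.

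**1. Reproducing 21, 24 and 72.** With three means whose extremes differ by d standard deviations and the third midway, f = d/√6. For d = 1, f = 0.408. In a parallel one-way ANOVA with n per group, λ = f² × 3n on 2 and 3n − 3 df:
- n = 20: power 79.3%
- n = 21: power 81.5%

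Then 21/0.9 = 23.3, rounded up to 24, and 24 × 3 = 72. The second paragraph therefore reproduces exactly, but as a parallel-group trial.

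**2. First paragraph, 0.10–0.13 read as Cohen's f.** For the within-person oil comparison, λ = f²Nm/(1 − ρ) = 6f²N on 2 and 2(N − 1) df.

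| f | N for 80% power | Power, N = 21 | Power, N = 65 | Power, N = 72 |
|---|---|---|---|---|
| 0.10 | 163 | 15% | 40% | 44% |
| 0.13 | 97 | 22% | 62% | 67% |

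At N = 72, for example, λ = 6 × 0.01 × 72 = 4.32 for f = 0.10 and 6 × 0.0169 × 72 = 7.30 for f = 0.13. With 65 completers and ρ from 0.3 to 0.7, power runs from about 30% to 61% at f = 0.10. At f = 0.13 it reaches 84% when ρ = 0.7, but the protocol sets ρ at 0.5.

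**3. Read as an SMD.** For a paired comparison the standardised difference is d/√(2(1 − ρ)), which equals d at ρ = 0.5. N for 80% power is 787 at 0.10 and 467 at 0.13. Power with 72 is 13% and 19%.

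**4. Read as partial eta-squared.** f = √(η²/(1 − η²)) gives 0.333 and 0.387. The oil comparison then needs 16 and 13 participants in total, and power with 72 exceeds 99%. On this scale SMD 1 is η² = 0.1667/1.1667 = 0.143, and 0.10–0.13 corresponds to a largest SMD of f√6 = 0.82 to 0.95. The two paragraphs would nearly agree.

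**5. Other routes to similar numbers.**
- η² = 0.10, 3 × 3 within-between interaction: 21 in total.
- η² = 0.10, three separate groups measured three times, between-group test: 61, rounded up to 63 = 21 × 3.
- f = 0.13 with all six measurements as one within-person factor: 65 in total. Power at 72 is 85% at f = 0.13 and 60% at f = 0.10.

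The first gives 21 people overall, not 21 per oil. The second compares separate groups of people. The third tests any difference among six visits (5 df), not the oils.

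**6. What 72 supports.** With 65 completers, the formula in step 2 gives 80% power at f = 0.159, a largest between-oil SMD of 0.159 × √6 = 0.39. At SMD 1 (f = 0.408), 12 participants in total would be enough.

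**The case against.** The metric of 0.10–0.13 is not stated, so a shortfall in power cannot be asserted outright. A reader might infer that the two effect sizes are incompatible, since SMD 1 is f = 0.41, three to four times 0.10–0.13, and that 80% power is simply not delivered. The document does not support either statement without a condition. On the eta-squared scale the two assumptions nearly agree, 72 is ample, and a total of 21 or a per-group 21 can be obtained from G*Power-type tests (step 5). Even on the f scale, a six-measurement analysis at 0.13 passes 80% with 72.

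This objection stands as far as it goes, and the power conclusion has to be conditional. Three things limit it. The words *minimal* and *conservative*, and the separate promise of a calculation at a medium effect, lean towards a small f, although that is inference and not proof. None of the alternative routes is the within-person comparison of three oils. And the mismatch between 24 × 3 and the cross-over does not depend on the metric at all.

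Nor can condensation into an article explain the problem: two calculations are printed, and they are not reconciled.

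**Conclusion.** Wrong as written. Without any assumption about the metric, two unreconciled calculations support one number, the scale of 0.10–0.13 is undefined, and 21 per group times three is parallel-group logic applied to a cross-over.

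The size of the power problem is conditional. If 0.10–0.13 is Cohen's f, the more natural reading, the stated 80% becomes about 40% to 62% with 65 completers. If it is an SMD, power is 13% to 19% even with all 72. If it is partial eta-squared, there is no shortfall, but 21 per oil times three still does not follow from the oil comparison. These figures rest on the assumptions listed with the inputs. Adjusting for nine primary markers would lower power.

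The number 72 is not itself shown to be wrong: it gives a cross-over able to detect an SMD of about 0.39 under those assumptions.

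**What to change.** Keep 72. State the metric, the test and the number of measurements behind 0.10–0.13. Replace both paragraphs with one cross-over calculation, for example: *72 randomised, about 65 completers, three periods, correlation 0.5, two-sided 5%: 80% power for f = 0.16 (largest between-oil SMD about 0.39).* That statement describes the design and holds whatever 0.10–0.13 turns out to mean.

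Remove the 24-per-period step and the factorial table. Only if 0.10–0.13 is confirmed as f, add that power there is about 40% to 62%. Writing those figures in before the metric is confirmed could introduce a new error.

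The cost is rewording one section, with no extra participants. The downside is that the stated power may become less favourable, in which case the Discussion's power claims for sex-stratified and gene-diet analyses would need to be toned down.

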### Blinding, randomization, and allocation concealment

The three intervention oils will be provided in the same shape, color, appearance, and odor and will be packed in the same bottles. Bottles will be blinded for researchers and participants and will be labeled with three codes (A, B, C) by an independent researcher. The codes will not be released until after the statistical analyses; therefore, neither the study participants nor the personnel nor the statisticians will be aware of the intervention oils. We do not anticipate any requirement for unblinding but if required, the trial manager and data coordinator will have access to group allocations and any unblinding will be reported.

We will use a stratified block (with a block size of 6) randomization in which the stratification will be done based on sex. Then, the participants in each block will be randomly assigned to one of the 6 sequences of the rolling process to consume the three intervention oils during the study period (ABC, ACB, BAC, BCA, CAB, or CBA; Fig. 1). To ensure that all the subjects receive treatments in a balance and random order, computer-generated random numbers will be used. The allocation sequence and randomization will be conducted by an independent researcher and will be concealed from the researchers. This will be done by putting the randomly assigned sequence of interventions for each participant in sealed opaque envelopes.

**Fig. 1 Fig1:**
[figure not shown]
The study flow chart. Participants will be randomized to six rolling processes to receive one of the intervention oils labeled as A, B, and C

### Intervention program

After the first visit, participants and their spouses will be entered into a run-in period for 4 weeks in which their regularly consumed oils will be replaced with sunflower oil. During the run-in period, the participants will be randomly assigned to one of the 6 rolling sequences (Fig. 1). The participants will be asked to replace the oils regularly used at home with the intervention oils. All measurements and blood sampling will be done at the beginning and the end of each intervention period, therefore, there will be 8 visits. The details of all measurements that will be conducted during each visit are provided in Table 1.

**Table 1 Tab1:** Details of study visits

Measured variables	Beginning of study	Beginning of the run-in period	Beginning of phase 1	End of phase 1	Beginning of phase 2	End of phase 2	Beginning of phase 3	End of phase 3
	Visit 1	Visit 2	Visit 3	Visit 4	Visit 5	Visit 6	Visit 7	Visit 8
**Eligibility criteria assessment**	*							
**Medical history**	*							
**Informed consent**	*							
**Nutrition counseling**	*							
**Medication use**	*	*	*	*	*	*	*	*
**Physical activity**	*	*	*	*	*	*	*	*
**24-h dietary recall**	*	*	*	*	*	*	*	*
**Anthropometric measurement**	*		*	*	*	*	*	*
Weight	*		*	*	*	*	*	*
Height	*		*	*	*	*	*	*
Waist circumference	*		*	*	*	*	*	*
Hip circumference	*		*	*	*	*	*	*
**Body composition indices**			*	*	*	*	*	*
Body fat mass			*	*	*	*	*	*
Lean mass			*	*	*	*	*	*
Visceral fat			*	*	*	*	*	*
**Blood pressure**	*	*	*	*	*	*	*	*
**Blood sampling**			*	*	*	*	*	*
**Biochemical assessment**			*	*	*	*	*	*
Fasting blood glucose (FBS)	*		*	*	*	*	*	*
Triglyceride (TG)	*		*	*	*	*	*	*
High-density lipoprotein (HDL)	*		*	*	*	*	*	*
Total antioxidant capacity (TAC)			*	*	*	*	*	*
Total oxidant status (TOS)			*	*	*	*	*	*
Malondialdehyde (MDA)			*	*	*	*	*	*
Myeloperoxidase (MPO)			*	*	*	*	*	*
Superoxide dismutase (SOD)			*	*	*	*	*	*
Catalase (CAT)			*	*	*	*	*	*
Glutathione peroxidase (GPX)			*	*	*	*	*	*
Glutathione reductase (GR)			*	*	*	*	*	*
Nitric oxide (NO)			*	*	*	*	*	*
**Compliance**								
Three-day food recalls			*	*	*	*	*	*
Weight measurement of intervention oils			*	*	*	*	*	*

All anthropometric measurements, dietary and physical activity assessments, and blood sampling will be also performed for the participant’s spouses. Their blood samples will be kept in our biobank for future analyses and biochemical analyses will be also done on spouses.

### Chemical analysis of intervention oils

For exploring the fatty acid content of intervention oils and sunflower oil, gas chromatography with a flame ionizer detector (GC-FID) will be used before their delivery [32]. Also, the total antioxidant capacity of the oils will be assessed by the diphenyl-1-picrylhydrazyl free radical (DPPH) method [33]. The time between the production of intervention oils and delivery to participants will be 1 to 2 weeks and will be consumed in 8 weeks.

### Primary and secondary outcomes

The primary outcomes will be changes in serum total antioxidant capacity (TAC) and total oxidant status (TOS), malondialdehyde (MDA), nitric oxide (NO), the enzyme activity of myeloperoxidase (MPO), superoxide dismutase (SOD), catalase (CAT), glutathione peroxidase (GPX), and glutathione reductase (GR). We will use standard ELISA kits for the measurements. Mean difference ± SD values from the baseline will be reported. The time-point for intervention periods will be 8 weeks. The secondary outcomes will be changes in body weight and body composition measurements (waist circumference, hip circumference, total body fat mass, muscle mass, visceral fat mass), as well as, blood pressure, fasting serum glucose levels (FBG), systolic and diastolic blood pressure (SBP and DBP, respectively), serum triglyceride levels (TG), and high-density lipoprotein cholesterol (HDL-cholesterol).

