### Statistical analyses

The statistical analysis will be performed using STATA software (version 14, TX, 77,845 USA). The normal distribution of the quantitative data will be determined using the Kolmogorov–Smirnov test, and the skewed variables will be normalized by transformation before analysis. The effects of treatment oils will be compared using the linear mixed method with the rolling process between-subject factors. Effect sizes will be adjusted by the potential confounders including age, sex, baseline BMI, the number of intervention oils consumed per subject, physical activity as metabolic equivalent-min/day, and the amount of calorie intake as covariates. Also, we will be performed subgroup analysis for sex. We will use the intention-to-treat method to handle protocol for those with non-adherence. No interim analysis is planned for this study because no early confirmatory conclusion of the effect of intervention oils can be drawn before the end of the study and enrollment of all participants. To control the carryover effect, clinically, an appropriate washout period will be considered (1 month). However, the carry-over effect will also be statistically tested through the mixed effect model. Any missing data will be handled using multiple imputations according to Harrell’s guidelines [36].

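### The stated analysis of changes lists no adjustment for each marker's own period baseline; adding it would sharpen the oil comparisons at no cost in samples or visits

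*Protocol article*

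**What the plan says.** In the protocol article, *Primary and secondary outcomes* sets the outcome scale. The definition opens "The primary outcomes will be changes in serum total antioxidant capacity (TAC", and eight further oxidative stress markers follow. The section adds that "Mean difference ± SD values from the baseline will be reported" and that "The time-point for intervention periods will be 8 weeks".

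*Intervention program* states that "All measurements and blood sampling will be done at the beginning and the end of each intervention period". Table 1 places the marker assays at Visits 3 to 8. Each participant therefore supplies six values of every marker, and each period has its own baseline (Visits 3, 5 and 7).

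*Statistical analyses* compares the oils with a linear mixed model. It names these covariates: age, sex, BMI at baseline, intervention oil consumed, physical activity and calories. The marker's own period baseline is not named, and the section does not say whether the dependent variable is the change or the end value.

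*Sample size* gives two effect sizes. Its first paragraph says "the minimal effect size of 0.10–0.13 as a conservative average was considered for primary outcomes", and that "a correlation between repeated measures as a conservative average was considered 0.5". Its second paragraph assumes a standardised mean difference of at least 1.

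**The concern.** In a cross-over trial each participant already serves as their own control. Subtracting a period baseline brings a second noisy measurement into every period's outcome. That costs precision unless the baseline is also allowed to enter with a fitted coefficient. A change score fixes that coefficient at 1. A baseline covariate lets the data choose it, and the best value is below 1 whenever the start and end of a period are imperfectly correlated.

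At stake is the precision of the oil contrasts on all nine primary markers. The blood samples that would recover it are already planned.

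**Working it through.** **Inputs.** Three periods with start and end values; 72 participants; 10% dropout, so 72 × 0.9 = 64.8, taken as 64 completers; power 80%; type I error 5%, taken as two-sided; one correlation of 0.5; effect sizes 0.10–0.13 (metric not named) and a standardised difference of 1. All come from *Sample size* and *Intervention program*. I assume the same SD σ at every visit.

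**The plan's own figure.** The protocol gives no variance for an oil contrast, so only the sample size can be reproduced.
- With a standardised difference of 1 and the error rate split over three comparisons, n = 2(2.394 + 0.842)² = 20.9, so 21 per group. A three-group one-way ANOVA with f = 1/√6 = 0.408 also gives 21. Then 21/0.9 = 23.3, so 24, and 3 × 24 = 72.
- Reading 0.10–0.13 as Cohen's f in a within-participant repeated-measures ANOVA with correlation 0.5, the requirement is 163 down to 97 people for three measures and 109 down to 65 for six.

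The stated 21/24/72 thus follows from the difference of 1. Both effect sizes are carried forward below.

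**Variance of an oil contrast, per person.** Let rw be the baseline-to-end correlation within a period and rb the correlation between any two measurements from different periods.
- Change scores: each change has variance 2σ²(1 − rw). Changes from different periods have covariance σ²(rb − rb − rb + rb) = 0. The contrast variance is 4σ²(1 − rw).
- Baseline-adjusted end values: the end-value difference and the baseline difference each have variance 2σ²(1 − rb), with covariance 2σ²(rw − rb). The within-person slope is r = (rw − rb)/(1 − rb), and the residual variance is 2σ²(1 − rb)(1 − r²).
- Since 1 − rw = (1 − rb)(1 − r), the ratio of the first to the second is **2/(1 + r)**, which exceeds 1 whenever r < 1.

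| rw | rb | Change | Adjusted | Ratio |
|---|---|---|---|---|
| 0.3 | 0.3 | 2.80 | 1.40 | 2.00 |
| 0.5 | 0.5 | 2.00 | 1.00 | 2.00 |
| 0.7 | 0.7 | 1.20 | 0.60 | 2.00 |
| 0.5 | 0.4 | 2.00 | 1.17 | 1.71 |
| 0.5 | 0.3 | 2.00 | 1.29 | 1.56 |
| 0.5 | 0 | 2.00 | 1.50 | 1.33 |
| 0.6 | 0.5 | 1.60 | 0.96 | 1.67 |
| 0.7 | 0.5 | 1.20 | 0.84 | 1.43 |
| 0.9 | 0.5 | 0.40 | 0.36 | 1.11 |

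(Variances in units of σ².) If correlation decays with time from 0.5 over 8 weeks, the ratio is 1.84 for adjacent periods and 1.44 for periods 1 and 3. Simulation with 72 people, six sequences and period effects gave 1.97 where theory says 2.00, and 1.53 where it says 1.56.

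**What this means for power, 64 completers, pairwise contrast.** With every correlation 0.5, the standard error is √(2/64) = 0.177σ for change and √(1/64) = 0.125σ adjusted. The difference detectable at 80% power is 2.80 times these: 0.495σ and 0.350σ. With evenly spaced means a Cohen's f corresponds to a largest difference of f√6, so 0.13 gives 0.318σ and 0.10 gives 0.245σ.

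| True difference | Change, all 0.5 | Adjusted, all 0.5 | Change, rw 0.7, rb 0.5 | Adjusted, rw 0.7, rb 0.5 |
|---|---|---|---|---|
| 0.318σ (f = 0.13) | 44% | 72% | 64% | 79% |
| 0.245σ (f = 0.10) | 28% | 50% | 43% | 57% |
| 1σ | >99% | >99% | >99% | >99% |

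The last two columns use standard errors √(1.20/64) = 0.137σ and √(0.84/64) = 0.115σ.

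**The case against.** **The covariate list is open and the full analysis plan is not shown.** The list is introduced as illustrative, the dependent variable is not named, and the sentence about means and SDs concerns reporting. A change outcome with the period baseline as a covariate gives the same oil estimate and variance as the adjusted end value, so calling the outcome a change costs nothing in itself. All of this stands, and it is why the point is an improvement and not an error. What remains is that the stated outcome and the stated covariates together describe an unadjusted change analysis, although the list does include the baseline of another variable.

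**A reader might infer that the plan's own correlation of 0.5 doubles the variance.** The document does not support this. It gives one value without saying which pairs of measurements it covers. The doubling comes from assuming equal correlations, and any common value produces it. If the 0.5 refers to the changes themselves across periods, the factor of 2 cannot be derived from it, because equal correlation of all six raw values would make those changes uncorrelated.

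**A reader might infer a definite loss of power.** The effect size of 0.10–0.13 has no named metric and is attached to outcomes defined as changes. If it is standardised by the SD of changes, their extra variance is already counted.

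**Two further arguments fail.** Changes can be negative, but "the skewed variables will be normalized by transformation before analysis" permits a marker to be logged first and differenced afterwards. Carry-over present at a period's start does enter the change score, but carry-over that persists to the period's end cancels from a change and stays in an end value. Neither argument decides between the two analyses.

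**The word baseline is not tied to a period.** If it meant one study-entry value, that value would cancel from within-person contrasts and add no variance. The 8-week time-point and the visit schedule make the period baseline the natural reading, though it is not written.

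**Conclusion.** The point holds as a free improvement. An unadjusted change score is unbiased under randomisation but less precise than a baseline-adjusted analysis of the same samples. The contrast variance is larger by 2/(1 + r): exactly 2 if all six measurements correlate equally, and about 1.1 to 1.8 in the cases tried where values within a period correlate more closely than values from different periods.

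The practical loss is negligible at a standardised difference of 1. It can be material at 0.10–0.13, where pairwise power differs by 14 to 28 percentage points in the two correlation structures worked through above. Those figures assume equal SDs, 64 completers, evenly spaced means, and Cohen's f on the scale of single values; the protocol confirms neither that metric nor the correlation structure.

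**What to change.** In *Statistical analyses*, name the dependent variable and the baseline adjustment:
- Analyse the end-of-period marker value or, equivalently, the change from the same period's baseline. Transform skewed markers before any differencing, and put the baseline covariates on the same scale.
- Fit the mixed model with oil, period and a random participant effect.
- Add the same period's marker baseline and the participant's mean marker baseline as covariates. Including the mean makes the period-baseline coefficient the within-person slope, so that it is not a mixture of within-person and between-person slopes.
- In *Primary and secondary outcomes*, say that the baseline is that of the same period, and keep mean ± SD changes as description.

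The cost is a few sentences and two covariates per marker model. All six blood samples are already scheduled; no visit, assay or participant is added.
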